## Abstract

**Background:**

Heart failure patients with implantable defibrillators (ICD) frequently visit the clinic for routine device monitoring. Moreover, in the case of clinical events, such as ICD shocks or alert notifications for changes in cardiac status or safety issues, they often visit the emergency department or the clinic for an unscheduled visit. These planned and unplanned visits place a great burden on healthcare providers.

Internet-based remote device interrogation systems, which give physicians remote access to patients' data, are being proposed in order to reduce routine and interim visits and to detect and notify alert conditions earlier.

**Methods:**

The EVOLVO study is a prospective, randomized, parallel, unblinded, multicenter clinical trial designed to compare remote ICD management with the current standard of care, in order to assess its ability to treat and triage patients more effectively.

Two-hundred patients implanted with wireless-transmission-enabled ICD will be enrolled and randomized to receive either the Medtronic CareLink^® ^monitor for remote transmission or the conventional method of in-person evaluations. The purpose of this manuscript is to describe the design of the trial. The results, which are to be presented separately, will characterize healthcare utilizations as a result of ICD follow-up by means of remote monitoring instead of conventional in-person evaluations.

**Trial registration:**

ClinicalTrials.gov: NCT00873899

## Background

Hospitalization for heart failure (HF) is an increasingly serious clinical issue and carries a heavy economic burden [1]. Thus, new strategies to keep HF patients out of hospital are needed.

Based on positive outcomes from numerous randomized controlled trials, the current guidelines for the management of chronic HF [1] include the use of implantable defibrillators (ICD) and defibrillators for resynchronization therapy (CRT-D) as the standard care in selected chronic HF patients.

The ability of implantable devices to continuously monitor variables such as heart rate [2], the patient's daily activity [3], intra-thoracic impedance for the detection of fluid accumulation [4], the occurrence of arrhythmias [5], and the integrity of the system [6] may provide early warning of changes in cardiac status or safety issues and allow early management. A standard method of notifying alert conditions in ICD uses a programmable feature that enables a patient to be audibly alerted if any of the various parameters exceeds the pre-defined range [7].

ICD patients visit the clinic for routine device monitoring 2–4 times per year [8,9]. However, many of these routine device checks result in no programming or device changes [10], and many patients suffer no clinically significant events between visits. When these patients do have clinical events, such as ICD shocks or device alert notifications, they often visit the emergency department (ED) or clinic for an unscheduled examination. These unplanned visits place an even greater burden on healthcare providers.

Several major manufacturers of devices offer a technology for remote ICD monitoring [11-13], with the purpose of reducing unnecessary routine and interim visits, and allowing physicians to remotely access patients' data.

Earlier detection and notification, combined with remote management, may also have the effect of shifting healthcare visits from the ED to the clinic, thereby reducing costs and the burden on the healthcare system. In addition, remote monitoring with these enhanced features may improve patients' quality of life by reducing anxiety between follow-up visits.

This study has been designed to compare these remote management capabilities with the current standard of care, in order to assess their ability to treat and triage patients more effectively.

## Methods/design

### The system

The Medtronic CareLink^® ^system (Minneapolis, MN, USA) includes a patient monitor plugged into a standard analog telephone connection, and a lightweight wand to communicate with the implanted device [11]. Interrogation of the device and transmission of the data occur when the patient places the wand over the implanted device. Moreover, the system uses radiofrequency telemetry for automatic wireless communication. This allows data transmission without patient intervention and enables automatic transmission at scheduled intervals as well as alert-based downloads. Specifically, in the case of programmable parameters, the system can transmit data on diagnostic variables, arrhythmias, ICD therapies delivered and battery/lead issues, and can alert the physician via phone or e-mail.

The patient's information is sent to a secure Network server via the telephone connection. The clinical staff can review device information on a secure Website via the Internet. Available data are equivalent to those which can be retrieved at an in-office visit.

### Hypothesis

It is hypothesized that patients implanted with ICD/CRT-D devices endowed with the CareLink system will require less attention for cardiac or device-related episodes than patients whose devices do not have such features.

### Objectives

The primary objective of the study is to determine whether patients using the CareLink system display a different rate of unplanned cardiac or device-related in-hospital visits from patients in the standard arm. The endpoints for this objective include all cardiac and device-related clinic visits, i.e. all hospital admissions not involving an overnight stay, when the interval between the decision to admit and the admission is <24 hours. The events anticipated to prompt these visits are: ICD alerts regarding system integrity, atrial and ventricular arrhythmias, decrease in intra-thoracic impedance signifying possible fluid accumulation, and patients' symptoms. These endpoints will be subdivided according to whether the visits are related or not related to episodes of worsening of HF; estimation of their respective rates will constitute a secondary objective of the study.

Additionally, the rate and related costs of total healthcare utilizations (all planned and unplanned hospital admissions involving and not involving an overnight stay) for cardiac or device-related events will be compared between groups. For this objective, hospital visits will be also scrutinized and classified as necessary or unnecessary for the clinical management of the patient. In particular, each visit will be judged necessary if it results from an appropriate and clinically meaningful ICD alert (e.g.: intra-thoracic impedance alert associated with clinically deteriorated HF) and if the clinician was not previously aware of the clinical/ICD condition.

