***Number of Shocks Delivered during an Episode***		

*Alert Enable – Device*	Off	Off

*Alert Enable – Monitor*	On	Off

*- Threshold Number of Shocks*	1	-

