***VF Detection/Therapy Off***		

*Alert Enable – Device*	On-High	On-High

*Alert Enable – Monitor*	On	Off

* For systems with an LV lead; ** For systems with dual-coil leads

In summary, all alerts regarding clinical management (intra-thoracic impedance for fluid accumulation monitoring, atrial arrhythmias, ICD shocks delivered) will be turned on for wireless notification through the CareLink in the remote arm, while no audible alerts will be used. In the standard arm these alerts will be turned on for audible notification only.

All lead and device integrity alerts will be turned on for both wireless and audible notification in the remote arm, and for only audible notification in the standard arm.

In the standard arm, audible alerts for intra-thoracic impedance monitoring will be programmed to sound at a different time of the day from alerts for other causes, in order to distinguish them.

Clinicians are allowed to turn off the alert for atrial arrhythmias, if they are no longer attempting to control the subject's atrial rhythm. Similarly, they can turn off the alert for intra-thoracic impedance when recurrent inappropriate detections of fluid accumulation are documented.

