### Management strategies

Clinics will be allowed to restrict notification of alerts to business hours, but will be encouraged to check the CareLink website at least once daily for transmissions.

If the clinic is notified of an audible alert sounding (both arms) or an alert received via CareLink (remote arm only), or if subjects report signs or symptoms, the clinician is required to implement management strategies that exploit the respective features available in the two arms. A summary of management strategy requirements is listed in Figure 2 for the standard arm, and in Figure 3 and 4 for the remote arm.

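### The rule for a necessary visit has no route for alert-free visits and gives no reference time for clinician awareness, so the label can depend on how the clinic was notified

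*Protocol article*

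**What the plan says.** The rule stands in the second paragraph of Objectives, under the comparison of rate and cost of all cardiac or device-related utilization, planned and unplanned, with or without an overnight stay. For that objective, "hospital visits will be also scrutinized and classified as necessary or unnecessary for the clinical management of the patient". The criterion follows: "each visit will be judged necessary if it results from an appropriate and clinically meaningful ICD alert", with the example "intra-thoracic impedance alert associated with clinically deteriorated HF", and "if the clinician was not previously aware of the clinical/ICD condition". The two conditions are joined by *and*. No other route to necessary is given.

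Four other places bear on how the rule works:

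- The first paragraph of Objectives lists what is expected to prompt unplanned visits. The list ends with "decrease in intra-thoracic impedance signifying possible fluid accumulation, and patients' symptoms", so symptoms are a trigger in their own right, beside the alerts.
- Under Device programming, the summary below Table 3 says that clinical management alerts "will be turned on for wireless notification through the CareLink in the remote arm, while no audible alerts will be used". In the standard arm they sound to the patient only. Lead and device integrity alerts in the remote arm go both ways.
- Under Management strategies, clinics may limit alert notification to business hours but "will be encouraged to check the CareLink website at least once daily for transmissions". The same section provides for the clinic being told of an audible alert in either arm.
- In Table 2, the row "Number of Shocks Delivered during an Episode" has the device alert Off in both arms, and the monitor alert On in the remote arm and Off in the standard arm.

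**The concern.** A label of necessary or unnecessary should say whether the patient needed the visit. This rule asks what set the visit off and what the clinician already knew.

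The first condition shuts out visits that the protocol itself expects. A patient who attends, or is admitted overnight, with symptomatic decompensation and no alert has no stated way to be counted as necessary, whatever was found or done.

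The second condition turns on clinician awareness, and earlier clinician awareness is what the remote arm is randomized to receive. Without a reference time, two assessors can label the same remote-arm visit in opposite ways. The trial is unblinded, so those choices could also differ by arm.

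At stake is whether the split can show that CareLink reduces avoidable visits, or partly reflects the route by which the clinic heard of the problem.

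**Working it through.** The plan gives no figure for this split, so the check is to apply the two conditions to each kind of visit in each arm. Condition 1 is a valid alert. Condition 2 is no previous awareness, read as (a) before the visit or (b) before the alert.

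| Visit trigger | Arm | Condition 1 | Condition 2, reading (a) | Condition 2, reading (b) |
|---|---|---|---|---|
| Symptoms, no alert | Both | Fails | Not reached | Not reached |
| Symptoms with an appropriate alert | Both | Can be met (the document's own example) | Depends on whether the clinic knew before the visit | Can be met |
| Clinical management alert | Remote | Can be met | Fails if CareLink was read before the patient was called in | Can be met |
| Clinical management alert | Standard | Can be met | Fails if the clinic was told of the audible alert before the visit; otherwise can be met | Can be met |
| Integrity alert | Remote | Can be met | Can be met if the patient attends on the sound before the transmission is read | Can be met |
| Shock | Remote | Can be met (monitor alert On, threshold 1) | Fails if CareLink was read first | Can be met |
| Shock | Standard | Not met by the shock alert under Table 2; can be met under the summary text | As for clinical management alerts, standard arm | Can be met if condition 1 is met |

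Four things follow.

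1. Symptom-only visits end as unnecessary in both arms under either reading.
2. The arms separate on awareness only under reading (a). Even then the separation is incomplete: a remote-arm clinic may not have read an out-of-hours transmission, and a standard-arm clinic may have heard of the audible alert before the visit.
3. Standard-arm shock visits cannot be classified from the text. Table 2 sets the shock alert Off there for both device and monitor. The summary below Table 3 counts delivered shocks among the alerts that are audible in that arm, and Rationale for design says that all alerts are audible there. Even if Table 2 governs, such a visit could meet condition 1 through another alert, such as the one for exhausted therapies, which Table 2 sets On for the device in that arm.
4. The possible distortions run in opposite directions. Reading (a) tends to move remote-arm visits into unnecessary; Table 2, taken alone, tends to move standard-arm shock visits there.

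On size, Sample size justification lists 140 + 34 + 6 + 40 = 220 planning episodes. Shocks are 40/220 = 18.2%; impedance and atrial arrhythmia episodes are 180/220 = 81.8%. These are episodes in CRT-D patients, not visits, so they show only that shocks are not a negligible trigger. The list has no symptom-only category, so the share of visits affected by the first condition cannot be derived from the document.

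**The case against.** The strongest reply has four parts.

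*The wording is softer than a strict definition.* The rule opens as a particular case and says *if*, not *only if*; the article condenses a fuller protocol that may hold the detailed classification. This stands in part: a fuller rule may exist. But a two-way split with one stated criterion leaves a reader no other basis for calling a visit necessary. The objection here is to the rule that is stated, not to detail that is absent.

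*Not previously aware may simply mean not already known before this alert*, which would exclude repeat alerts for a known problem. That is at least as natural a reading, and under it CareLink notification disqualifies nothing. This stands. What remains is that the text does not choose.

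*The arm contrast is not established.* A reader might infer that remote-arm visits always fail the rule while the same deterioration in a standard-arm patient passes. The document does not support that. It needs reading (a), CareLink review before every visit, and no prior notice of audible alerts in the standard arm; Management strategies and the integrity-alert settings allow exceptions to each of the last two. A reader might also infer that symptomatic visits can never qualify, but the document's own example pairs an alert with clinical deterioration.

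*The consequence is limited.* The primary rate of unplanned visits does not use the label, and no test of the split is specified. This stands and bounds the importance of the point.

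**Conclusion.** The concern holds in limited form. Two defects are clear from the text: visits without an alert have no stated route to necessary, although symptoms are an expected trigger, and the awareness condition has no reference time. A third is a conflict to be reconciled: Table 2 against the summary below Table 3 and Rationale for design, on whether shocks raise an alert in the standard arm.

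Together these mean that the label can depend on the notification route rather than on need. Neither the number of visits affected nor the net direction of bias can be stated; a systematic bias against the remote arm is not shown. The damage is confined to the necessary/unnecessary split under the total-utilization objective. Total rates and costs, which do not need the label, and the primary endpoint are untouched.

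This rests on taking the stated criterion as the operative one. If the full protocol holds a broader definition, the article's wording should be aligned with it.

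**What to change.** - Define necessity in the same way in both arms by what the visit found or led to, such as a change of treatment, device reprogramming, an intervention, an admission or a finding that called for assessment in person. Apply it whatever the trigger: alert, shock or symptom.
- Give awareness a reference time: it counts only if the condition was known before the alert or symptom that triggered that episode. CareLink notification of the same episode then does not disqualify a visit.
- Reconcile Table 2 with the summary below Table 3 and Rationale for design on the standard-arm shock alert, so that it is clear what those visits can result from.
- Where feasible with existing staff, have visits classified without knowledge of arm, from summaries with the notification route removed.

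The cost is one reworded definition and somewhat more work per visit. What was found or done must come from the healthcare-utilization records, because Table 1 schedules medications only at baseline and 16 months. The sponsor should check that those records hold enough detail. Some judgement will remain in deciding what needed assessment in person, which is a further reason to conceal the arm.

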### Other variables

This study will also test whether the CareLink system:

• Reduces the time between the onset of asymptomatic events and the clinical decision on such events;

• Modifies the degree of patient anxiety, as measured by the composite scores of both the State and Trait components of the State-Trait Anxiety Inventory – Form Y;

• Modifies the patient's clinical status, as measured by the Clinical Composite Score [14];

• Modifies the patient's quality of life, as measured by the Minnesota Living with Heart Failure Questionnaire and the EQ-5D Questionnaire.

### Design

This is a one-to-one randomized, prospective study. The study has been approved by the Institutional Review Board of the 6 participating Italian centers.

Patients implanted with wireless-transmission-enabled Medtronic ICD or CRT-D will be randomized to "remote transmission on" (remote arm) or "remote transmission off" (standard arm) (Figure 1).

**Figure 1 F1:**
[figure not shown]
**Trial design**. Enrollment and follow-up schedule.

Randomization will be stratified by center and by time from implantation (≤ 6 months and > 6 months) to minimize selection bias and preserve homogeneity between arms with regard to stability of clinical status.

In the remote arm, devices will be programmed to transmit over the CareLink Network. Devices in the standard arm will have all features available in their ICD/CRT-D, including the audible notification of alerts, but will not have access to the CareLink Network.

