**Figure 4 F4:**
[figure not shown]
**Management strategy requirements**. Operative flowcharts for the management of atrial fibrillation alerts in the remote arm.

Assessment of the patient's clinical status and verification of appropriate functioning of the ICD will be performed in accordance with the current guidelines and the center's routine practice.

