### Statistical methods

An intention-to-treat analysis will be performed on all randomized subjects and will serve as the primary analysis for all objectives in this study.

The primary and secondary hypotheses will be tested by using the Comparison of Incidence Rates (Large Sample) Test. A two-sided test and a significance level of α = 0.05 will be used.

Cost analysis will be carried out from the perspectives of the healthcare system and the patient. Consequently, the unit costs considered will be related to the public tariffs or to the patient's out-of-pocket expenses. The in-hospital resources related to the introduction and utilization of CareLink will also be evaluated.

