Other trials have used a control arm blinded to device data [22], in order to test the clinical value of diagnostic features. By contrast, in the present study all alerts will be turned on for audible notification in the standard arm and the diagnostics will be open for in-office review. This will enable the benefits associated to remote notification and access to ICD data to be specifically assessed in addition to the diagnostic and alerting capabilities of modern ICD.

Another trial is currently investigating the CareLink system in pacemaker patients [23]. The present study on ICD/CRT-D patients, however, will focus on a sicker population with more complex devices. This is the setting in which remote monitoring is presumed to offer the greatest benefits.

In the hypothesis of a more stable clinical status of the patient and a reduced need to adjust ICD parameters 6 months after implantation [10], stratifying patient randomization on the basis of time since implantation will limit a potential bias.

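### The named rate test omits the randomisation strata: nearly harmless with an event-count variance, but a modest loss of power once the variance is estimated at patient level

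*Protocol article*

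**What the plan says.** Under Design, in the text beneath Figure 1, the protocol article says: "Randomization will be stratified by center and by time from implantation (≤ 6 months and > 6 months"). The same section says: "The study has been approved by the Institutional Review Board of the 6 participating Italian centers". Six centres by two time bands give 12 cells.

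Rationale for design supposes that patients are clinically more stable beyond six months from implantation, and concludes that "stratifying patient randomization on the basis of time since implantation will limit a potential bias". Centres also keep some latitude. Management strategies lets clinics confine alert notification to business hours, and has patient assessment and device checks done "in accordance with the current guidelines and the center's routine practice".

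Statistical methods then fixes the analysis: "The primary and secondary hypotheses will be tested by using the Comparison of Incidence Rates (Large Sample) Test". It adds: "A two-sided test and a significance level of α = 0.05 will be used". Neither that section nor Sample size justification mentions the strata. The article does not say that they will be used, nor that they will be ignored. It gives no event rates by centre or by time from implantation.

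**The concern.** Stratified randomisation makes the arms alike on the chosen factors. If those factors predict the visit rate, the treatment comparison is more precise than an unstratified patient-level analysis recognises. Such an analysis leaves the between-cell spread in its standard error although the design has removed it from the comparison. The test is then conservative and loses power.

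Whether this applies depends on where the variance comes from. An event-count (Poisson) variance does not contain the between-cell spread; a variance estimated from the scatter between patients does. The primary endpoint counts all qualifying visits, so one patient can contribute several, and that calls for the second kind.

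**Working it through.** **Inputs from the article.** 100 patients per arm, 16 months of follow-up, 20% dropout spread uniformly, 2.2 events per person-year, two-sided α 0.05, planned rate ratio 0.90, 12 cells (200/12 ≈ 17 patients each). Person-years per arm = 100 × 16/12 × (1 − 0.20/2) = 120. Control-arm events = 120 × 2.2 = 264.

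**Assumptions, not in the article.** Centre SD of log rate 0.2 to 0.6; 1.5-fold rate difference between implant-time bands (1 to 2 in step 2); between-patient variance 0.5; rate ratio 0.65 or 0.70.

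**Step 1: the article's own power figure.** For a rate ratio of 0.90 the SE of the log rate ratio is √(1/264 + 1/237.6) = 0.0894, so z = 0.1054/0.0894 = 1.178 and power = Φ(1.178 − 1.960) = 21.7%. The stated 99.8% does not reproduce. That is a separate matter, unrelated to strata.

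**Step 2: the named test with event-count variance.** At rate ratio 0.70, SE = √(1/264 + 1/184.8) = 0.0959, z = 0.3567/0.0959 = 3.72 and power = 96.1%. Between-cell spread does not enter this SE. Simulation (8,000 trials per setting, permuted blocks of 4 in 12 cells, no patient-level dispersion) gives, unstratified / stratified:

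| Centre SD, implant-time ratio | Type I error | Power at 0.90 | Power at 0.70 |
|---|---|---|---|
| 0, 1 | 4.9% / 4.9% | 22.0% / 21.7% | 96.5% / 96.4% |
| 0.2, 1.25 | 4.9% / 4.8% | 21.7% / 21.5% | 96.0% / 96.2% |
| 0.4, 1.5 | 5.9% / 5.3% | 22.5% / 21.9% | 95.5% / 95.9% |
| 0.6, 2 | 6.5% / 4.9% | 22.7% / 21.2% | 95.6% / 96.0% |

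The power difference at 0.70 is under half a point. At 0.90 stratifying gains nothing.

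**Step 3: patient-level variance, by hand at centre SD 0.4.** The variance of an arm's log rate is about 1/events + kV/100. V is the relative variance of patient rates. k allows for unequal follow-up: (0.8 + 0.2/3)/0.9² = 1.070.

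- Between cells: centre ≈ 0.4² = 0.16; implant time (rates 1 and 1.5 in equal halves) = (0.25/1.25)² = 0.04; together 1.16 × 1.04 − 1 = 0.206.
- V ignoring cells = 1.5 × 1.206 − 1 = 0.810. V within cells = 0.5 × 1.206 = 0.603.
- At rate ratio 0.65 the count part is 1/264 + 1/171.6 = 0.00962.
- Estimated SE without strata = √(0.00962 + 2 × 0.810 × 1.070/100) = 0.1641. Actual SE with balanced cells = √(0.00962 + 2 × 0.603 × 1.070/100) = 0.1501.
- Power without strata = Φ((0.4308 − 1.960 × 0.1641)/0.1501) = Φ(0.727) = 76.6%. With strata = Φ(0.4308/0.1501 − 1.960) = Φ(0.910) = 81.9%.
- Under the null the two SEs are √(2/264 + 0.01733) = 0.1578 and √(2/264 + 0.01290) = 0.1431. Type I error without strata = 2Φ(−1.960 × 0.1578/0.1431) = 3.1%.

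This takes balance as perfect. Incomplete blocks and dropout soften it a little, as the simulations show.

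**Step 4: simulation with patient-level variance.** Implant-time ratio 1.5, patient variance 0.5, rate ratio 0.65; without / with strata:

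| Centre SD | Type I error, log-linear model (4,000 trials) | Power, same | Type I error, Mantel-Haenszel (2,000 trials) | Power, same |
|---|---|---|---|---|
| 0.2 | 4.7% / 5.3% | 85.6% / 87.8% | 4.4% / 5.3% | 82.5% / 84.6% |
| 0.4 | 3.7% / 5.4% | 80.8% / 85.5% | 4.3% / 5.7% | 78.2% / 83.2% |
| 0.6 | 3.4% / 6.0% | 73.8% / 82.1% | 3.2% / 5.4% | 72.0% / 80.8% |

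The gains are 2.2, 4.7 and 8.3 points in the first set and 2.1, 5.0 and 8.8 in the second. With no stratum effect the Mantel-Haenszel comparison gave 86.0% / 86.2%, so including the strata lost no power.

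**Step 5: how much of the gain is excess type I error.** At SD 0.6 the stratified log-linear test runs at 6.0%, for which the critical value is 1.881. Holding it to 5% shifts z by 1.960 − 1.881 = 0.079. Power of 82.1% (z = 0.919) becomes Φ(0.840) = 80.0%, so the gain falls from 8.3 to 6.2 points. The same step gives 3.9 points at SD 0.4 and 1.7 at SD 0.2.

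**The case against.** The strongest reply is that the article merely names a test in one sentence. Articles commonly leave stratum terms to the full protocol or the analysis plan, neither of which is shown, and a Mantel-Haenszel comparison is itself a comparison of incidence rates. This stands in part. A reader might infer that the plan has decided to ignore the strata; the article says no such thing. What remains is that it commits all primary and secondary hypotheses to a named two-rate test that, as named, does not reflect the design.

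Second, the named test with event-count variance loses almost nothing, and its miscalibration is slightly anti-conservative rather than conservative. Step 2 bears this out in full. A reader might infer that the test as written gives away power; it does not. The loss arises only once the variance is corrected for repeat visits.

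Third, the strata are justified as a guard against bias and a way to keep the arms alike. Only time from implantation is linked to clinical stability, and only as a hypothesis; nothing says that rates are expected to differ by centre. That is fair, and it is why every size given here is conditional. Part of the simulated gain is also excess type I error (Step 5).

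**Conclusion.** The point holds as a modest improvement to a stated method. Under a patient-level variance, omitting the strata makes the test conservative (about 3% to 5% instead of 5%) and costs roughly 2 to 9 points of power, or about 2 to 6 in the log-linear runs after holding the stratified test to its nominal level. The loss is near zero if the strata do not predict the visit rate. The range rests wholly on the assumed centre SD, implant-time difference, patient variance and rate ratio.

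A reader might also infer that stratifying would cure the inflation that repeat visits cause in the event-count test. It would not. In simulation that test's type I error was 21% to 25% at patient variance 0.5. At patient variance 1 it was 31% to 39%, with or without strata. Only a patient-level variance repairs that, so the two changes belong together.

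**What to change.** State in Statistical methods that the primary and secondary visit rates will be analysed with centre (six levels) and time from implantation (two levels) as terms in a rate model, or by a Mantel-Haenszel rate ratio over the 12 cells. In either case use a variance estimated at patient level, and report the crude rate ratio as supportive. If the full protocol or analysis plan already says this, a cross-reference is enough.

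With 12 cells and 200 patients the robust stratified test can run slightly high (about 5% to 7% in simulation), so name a small-sample correction in advance. It will take back a little of the gain.

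Table 1 collects healthcare utilisation at baseline. Adjusting for it is optional, and the gain cannot be sized from the article.

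The cost is wording. No new data are needed, since both factors are known at randomisation.
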